## Abstract

**Background:**

Post COVID-19 syndrome, defined as the persistence of COVID-19 symptoms beyond 3 months, is associated with a high emotional burden. Post COVID-19 patients frequently present comorbid anxiety, depressive and related disorders (emotional disorders, EDs) which have an important impact on their quality of life. Unfortunately, psychological interventions to manage these EDs are rarely provided to post COVID-19 patients. Also importantly, most psychological interventions do not address comorbidity, namely simultaneous EDs present in COVID-19 patients. This study will explore the clinical utility and acceptability of a protocol-based cognitive-behavioral therapy called the Unified Protocol for the transdiagnostic treatment of EDs in patients suffering post COVID-19 condition.

**Methods:**

A multiple baseline n-of-1 trial will be used, as it allows participants to be their own comparison control. Sample will be composed of 60 patients diagnosed with post COVID-19 conditions and comorbid EDs from three Spanish hospitals. After meeting the eligibility criteria, participants will answer the pre-assessment protocol and then they will be randomly assigned to three different baseline conditions (6, 8, or 10 days of assessments before the intervention). Participants and professionals will be unblinded to participants’ allocation. Once the baseline assessment has been completed, participants will receive the online psychological individual intervention through video-calls. The Unified Protocol intervention will comprise 8 sessions of a 1 h duration each. After the intervention, participants will answer the post-assessment protocol. Additional follow-up assessments will be conducted at one, three, six, and twelve months after the intervention. Primary outcomes will be anxiety and depressive symptoms. Secondary outcomes include quality of life, emotion dysregulation, distress tolerance, and satisfaction with the programme. Data analyses will include between-group and within-group differences and visual analysis of patients’ progress.

**Discussion:**

Results from this study will be disseminated in scientific journals. These findings may help to provide valuable information in the implementation of psychological interventions for patients suffering post COVID-19 conditions.

**Clinical trial registration:**

https://clinicaltrials.gov, identifier (NCT05581277).

## Introduction

1.

In December 2019, the COVID-19 disease was originated in Wuhan (China) and currently it is considered one of the greatest pandemics ever. According to the data reported by the World Health Organization (WHO), it is estimated that 657 millions of people worldwide have contracted the infection and more than 6 millions of people have died, which has had an impact in 220 countries (WHO, 2022a).

The symptoms more frequently reported in patients with COVID-19 infections include, but are not limited to, fever, cough, tiredness, loss of taste or smell, sore throat, headache, and shortness of breath (WHO, 2021). While most COVID-19 patients recover from these symptoms, it is also well-known that an important proportion of patients get no relieve from COVID-19 symptoms, a condition known as post COVID-19 condition or long COVID-19. By definition, patients who continue to experience or develop new symptoms of COVID-19 three months after contracting COVID-19 are diagnosed as long COVID patients (WHO, 2022b). Nowadays, it is difficult to determine the precise prevalence of post COVID-19 conditions in COVID-19 survivors, but estimations establish that around 10–20% of people infected by the virus develop long COVID-19 condition (WHO, 2022b).

Aside from the physical consequences, the pandemics itself and the subsequent restriction measures (i.e., lockdown, reduction of social contact, job instability, and economic difficulties) have had an impact on the psychological wellbeing of the general population (Liu et al., 2021). A recent meta-analysis with 146,139 participants from nine different countries found that the most common symptoms during the COVID-19 crisis were emotional disorders, namely anxiety, depressive and related disorders (hereafter EDs; Barlow et al., 2018). This meta-analytic study found high prevalence rates of anxiety (32.60%), insomnia (30.30%), depression (27.60%) and post-traumatic stress disorder (16.70%) with increased prevalence of EDs in patients with suspected and confirmed COVID-19 infection (63.90% reported anxiety symptoms and 55.40% depressive symptoms; Liu et al., 2021).

In the particular case of patients suffering post COVID-19 conditions, the most frequently reported psychological problems were also anxiety (22.20%) and depressive disorders (21.10%; Deer et al., 2021). Apart from this, patients suffering long COVID conditions may be at increased risk of ED chronification as they may have to cope not only with physical symptoms but also with loneliness and the stigma related to scepticism about their symptoms, which may in turn compromise their social and family life, work functionality and quality of life (Brown and O’Brien, 2021; Office of National Statistics, 2021).

In light of the aforementioned psychological negative consequences of the pandemic, it might be reasonable to think that patients with COVID-19, and especially those with long COVID-19, would receive evidence-based psychological interventions to overcome EDs. Different systematic reviews indicated that psychological interventions are available in the context of COVID-19 for the general population and students (D’Onofrio et al., 2022; Komariah et al., 2022), professionals and informal caregivers (Bertuzzi et al., 2021), relatives (Yue et al., 2020), or even COVID-19 patients (Rahmati and Khalili, 2022). Results from these systematic reviews indicate that psychological interventions could be effective in the management of EDs in the context of COVID-19 conditions, however, some needs are not properly addressed. First, few studies are focused on specific long COVID-19 patients. To the best of our knowledge, only one study (Bogucki and Sawchuk, 2022) provided a Cognitive Processing Therapy to manage Post Traumatic Stress Disorder in a female patient with recurrent COVID-19 infections and a diagnosis of post COVID-19 condition. Second, specific symptom-based interventions are usually provided (Chennapragada et al., 2022), which makes it difficult to address comorbid EDs, for instance, anxiety and depressive symptoms that are simultaneously present in COVID-19 patients (Joli et al., 2022).

As an alternative to symptom-focused approaches, different transdiagnostic therapies have emerged during the last decades. The Unified Protocol (UP) for the transdiagnostic treatment of EDs (Barlow et al., 2018) is one example of a transdiagnostic cognitive-behavioral psychological intervention focused on training in adaptive emotion regulation skills. Contrary to previous psychological interventions, the UP is not focused on specific symptoms associated with different disorders if not on shared factors, for example neuroticism, which can explain the development and maintenance of these emotional disorders. Neuroticism has been defined as the tendency to experience unpleasant emotions (anxiety, fear, irritability, sadness, etc.) frequently and intensely in response to different sources of stress (Barlow et al., 2014), and has been shown to underlie the origin of EDs, as well as the high comorbidity present in these disorders (Brown and Barlow, 2009). Therefore, intervening on this mechanism would allow us to address through a single treatment, a wide number of disorders (Barlow et al., 2014).

Recent systematic reviews and meta-analysis evidence that the UP could help to manage EDs in the general population (Sakiris and Berle, 2019; Cassiello-Robbins et al., 2020; Carlucci et al., 2021; Longley and Gleiser, 2023) and also in individuals with comorbid medical conditions such as those living with Human Immunodeficiency Virus (HIV), cancer, chronic pain or multiple sclerosis, among others (Osma et al., 2021). Also importantly, it has been proposed that emotion regulation could act as a transdiagnostic mechanism for mental health in the context of COVID-19 (Volkert et al., 2021) thus it could be reasonable to think that training in emotion regulation skills (i.e., practicing emotion awareness, cognitive flexibility, emotion driven behaviors and expositions) may result in the improvement of clinical symptomatology (i.e., anxiety and depressive symptoms) in that patients. However, one of the main research problem is that to the best of our knowledge, no UP-based intervention has been implemented in the specific population of long COVID-19 patients.

With the aforementioned information in mind, there is no doubt that psychological interventions for the treatment of psychological sequelae derived from post COVID-19 condition are urgently needed. The present manuscript describes the study protocol of a multiple baseline n-of-1 trial that aims to study the clinical utility and acceptability of the “Unified Protocol for the Transdiagnostic Treatment of Emotional Disorders” in the treatment of EDs and/or symptoms in a sample of patients with post-COVID-19 condition. Our hypothesis is that a structured UP-based psychological intervention focused on treating emotional dysregulation will be effective in the improvement of EDs and/or symptoms in a sample of patients with post COVID-19 conditions. More precisely, we expect that all outcomes’ measures (i.e., anxiety, depression, emotion dysregulation, quality of life and distress) will significantly improve from pre- to post-assessment. Additionally, we hypothesized that these improvements will be maintained long term (follow-up at one, three, six, and twelve months after the intervention). Finally, our hypothesis is that excellent acceptability (i.e., adherence rates) and satisfaction with the contents and format of the intervention will be found.

## Methods and analysis

2.

### Design

2.1.

This protocol describes the procedures of a pilot study which uses multiple baseline single case design to explore the preliminary clinical utility and acceptability of the UP in the treatment of EDs or symptoms in a sample of patients with post COVID-19 condition. This trial has been previously registered in clinicaltrials.gov on October 14th, 2022 and updated on January 20th, 2023 (NCT05581277). The present protocol follows the SPENT checklist (SPIRIT extension for N-of-1 trials; Porcino et al., 2020) that can be consulted in Supplementary material A (SPENT checklist) and B (abstract checklist).

Multiple baseline single case design is frequently used in clinical settings to explore the effect of an intervention on a reduced group of patients (Kazdin, 2011). It is selected for this trial as no control group is needed because each participant acts as their own control comparison (Kratochwill et al., 2012). Current guidelines recommend three different baseline conditions with at least 3–5 data points in each group (Kratochwill et al., 2010, 2012). Accordingly, we will assign participants to three different baseline conditions: 6, 8 and 10 days of assessments prior to the beginning of the intervention. Participants will by randomly allocated to one of the three baseline conditions.

### Participants

2.2.

#### Eligibility

2.2.1.

This is a secondary study derived from a bigger project called “ARACOV.” Participants in our study will be composed of a subsample of the ARACOV multicentre project. The ARACOV project aims to characterize patients with long COVID-19 and assess the impact of a nutritional and rehabilitation intervention for the improvement of quality of life in a cohort of patients with post COVID-19 condition. According to the procedures of this project, participants with long COVID-19 that are interested in participating in the project ARACOV will contact recruiting nurses. In this step nurses will conduct an extensive interview to explore if patients are able to participate in this primary ARACOV project. Patients who are not included in this specialized nutritional intervention and rehabilitative treatment due to exclusion criteria (see supplementary material C) would be offered the possibility of participating in the secondary study that aims to implement a transdiagnostic psychological intervention. Eligibility criteria to participate in this transdiagnostic psychological intervention include: being long COVID-19 adult patients (over 18 years old), presenting emotional disorders or symptoms and residing in the autonomous community of Aragón (see Table 1).

**Table 1 tab1:** Eligibility criteria to participate in the present study based on the application of a psychological transdiagnostic intervention.

Inclusion	Exclusion
Enough understanding of Spanish. Documented COVID-19 infection (i.e., PCR, Ag test or serology). Presenting Post COVID-19 condition (i.e., persistence of COVID-19 symptoms beyond 12 weeks after the initial infection). Anxiety or depressive symptoms (OASIS Score equal to or greater than 8 points or ODSIS scores equal to or greater than 7 points) and/or diagnosis of emotional disorders according to ADIS-5 interview. Having Internet access. Signing informed consent.	Participating in the trial “Specialized nutritional intervention and rehabilitative treatment for improvement of quality of life in a cohort of patients with post COVID-19 condition” from the ARACOV-01 project. Symptoms were present prior to acute COVID-19 infection. Currently receiving psychological and/or pharmacological treatment for mental health issues. Having a severe mental health disorder (e.g., bipolar and related disorders, schizophrenia and related disorders, feeding and eating disorders, dissociative disorders, etc.). Active suicidal ideation at the time of first evaluation.

PCR, polymerase chain reaction; ADIS-5, anxiety and related disorders interview schedule for DSM-5; OASIS, overall anxiety severity and impairment scale; ODSIS, overall depression severity and impairment scale.

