**Figure 1 fig1:**
[figure not shown]
Flow chart of participants and procedures.

Participants who meet the inclusion criteria (Table 1) will be given the information sheet and will sign the informed consent in the face-to-face consultation with the nursing team. Then, the psychologist of the study ([name]) will contact participants by telephone and will arrange an online session through a video-call to assess EDs according to the Anxiety and Related Disorders Interview Schedule for DSM-5 (ADIS-5; Brown and Barlow, 2014) which would also help to explore if any exclusion criteria are present (i.e., participants present a severe mental health issue or current suicidal ideation). Patients who meet any of these exclusion criteria will be recommended to consult with their mental health service of reference. If inclusion criteria are accomplished, participants will receive the pre-assessment protocol through e-mail and they will answer the questionnaires via the online platform Google Forms. Once the pre-assessment is completed, each participant will be sequentially and randomly assigned to one of the three multiple baseline conditions (Condition 1: 6 days of baseline assessments; Condition 2: 8 days of baseline assessments; Condition 3: 10 days of baseline assessments). During the baseline period, participants will receive daily e-mails with the online baseline assessment to be answered through Google Forms. Randomization to different baseline conditions will be conducted with a computer-generator online software (www.randomizer.org). An independent researched not involved in the implementation of the psychological intervention will sequentially assign participants to the three baseline conditions. Participants and professionals will know the baseline condition to which patients have been assigned.

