### Outcomes

2.4.

The assessment protocol of the study includes nine assessment points (eligibility, baseline, pre-assessment, during treatment, post-assessment and four follow-ups). Table 2 shows the measures used in each phase of the study.

**Table 2 tab2:** Measures administration during the different phases of the trial.

Outcome	Eligibility	Pre	Baseline	Treatment	Post	Follow-ups
ADIS-5	X					
Sociodemographic	X					
COVID-19 symptoms	X					
OASIS		X	X	X	X	X
ODSIS		X	X	X	X	X
MEDI		X			X	X
EuroQol-5D		X			X	X
DERS		X			X	X
DTS		X			X	X
CSQ-8					X	
UP-satisfaction					X	

Pre, pre-assessment; Post, post-assessment; ADIS, anxiety and related disorders interview schedule for DSM-5; OASIS, overall anxiety severity and impairment scale; ODSIS, overall depression severity and impairment scale; MEDI, the multidimensional emotional disorder inventory; EuroQol-5D, health-related quality of life; DERS, difficulties in emotion regulation scale; DTS, distress tolerance scale; CSQ-8: client satisfaction questionnaire; UP: Unified Protocol.

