#### Primary outcomes

2.4.1.

Sociodemographic: sex, age, place of residence, marital status, employment status, healthy habits (i.e., smoking, alcohol, physical activity, diet), SARS CoV 2 vaccination. Sociodemographic variables will be evaluated to characterize the sample.COVID-19 symptoms: symptoms of post COVID-19 condition referred by the patient according to 10 categories: General, respiratory, gastrointestinal, musculoskeletal, cutaneous, otolaryngological, neurological, cardiovascular, psychological and other symptoms. COVID-19 characteristics will be assessed to describe the sample.Overall Anxiety Severity and Impairment Scale (OASIS; Norman et al., 2006; Osma et al., 2021): it consists of 5 items assessing frequency of anxiety symptoms, severity of anxiety symptoms, avoidance and interference. Higher scores indicate more severe anxiety symptoms. Good internal consistency was found in the Spanish version of this instrument (α = 0.87; Osma et al., 2021).Overall Depression Severity and Impairment Scale (ODSIS; Bentley et al., 2014; Osma et al., 2021): it comprises 5 items assessing frequency of depressive symptoms, severity of depressive symptoms, anhedonia and interference. Higher scores represent more severe depressive symptoms. Excellent internal consistency was found in the Spanish version of this instrument (*α* = 0.94; Osma et al., 2021).Anxiety and Related Disorders Interview Schedule for DSM-5 (ADIS-5; Brown and Barlow, 2014): it is a structured clinical interview to diagnose current anxiety, mood and related disorders (i.e., obsessive-compulsive, trauma, somatic symptoms, substance use) according to the Diagnostic and Statistical Manual of Mental Disorders criteria (5th edition, DSM-5; American Psychiatric Association, 2013). Different editions of the ADIS have shown good reliability with good-to-excellent interrater agreement for DSM disorders (Brown and Barlow, 2014). In this trial, this interview will be used to assess eligibility criteria to participate in the trial.Adjustment disorders: adjustment disorders are usually accompanied by medical illness (American Psychiatric Association, 2013). Given the high prevalence of adjustment disorders in the context of the COVID-19 pandemic, and specially in people who experience COVID-19 stressful situations (Ben-Ezra et al., 2021), participants in this trial will be assessed for the presence of adjustment disorders according to DSM-5 criteria (American Psychiatric Association, 2013).

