### Data analysis

2.6.

The Statistical Package for the Social Sciences (SPSS) version 22.0 for windows (IBM Corp, 2013) will be used to conduct the statistical analysis.

First, normal distribution test will be conducted to explore whether the data obtained followed a normal distribution. According to the distribution of the sample, we will use parametric or non-parametric analyses. Then, descriptive data (mean, standard deviation, and proportions) of all study variables will be reported in order to characterize the sample (i.e., sociodemographic and psychosocial status). Missing-value analysis and the Little Missing Completely At Random test (MCAR) will be used to check whether missing values are randomly presented. Last observation carried forward (LOCF) will be used in this case (Jakobsen et al., 2017).

Analysis of Variance (ANOVA), or its equivalent non-parametric Friedman test, will serve to test whether there are differences between the three baseline conditions at pre-assessment to ensure that randomization resulted in comparable groups. Repeated measures ANOVA will help to determine if between-group (differences in outcome variables between the three baseline conditions at different assessment points) and within group differences (differences between the pre-treatment and the remaining assessments in the outcome variables for each baseline condition) are present. Additionally, effect sizes (Cohen’s *d*) will be calculated for both between and within group analyses. Effect sizes will be interpreted as small (*d* ≈ 0.2), medium (*d* ≈ 0.5) or large (*d* ≈ 0.8).

As recommended for n-of-1 trials, visual analysis of the data by graphs will also be used to determine whether the psychological outcomes improve as a consequence of intervention contents. By doing so, we will establish the baseline pattern on OASIS and ODSIS scales and compare it with the data within the following treatment phase and also with results obtained during the follow-up assessments. The statistical Software R version 4.1.0 (R Core Team, 2021) will be used for the graphical representation of slopes.

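### The OASIS/ODSIS pre-post contrast starts before the untreated baseline days, and Table 2 schedules no administration for the entry cut-offs

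*Protocol article*

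**What the plan says.** **Entry.** Table 1 (section 2.2.1) gives two routes into the trial: "Anxiety or depressive symptoms (OASIS Score equal to or greater than 8 points or ODSIS scores equal to or greater than 7 points", joined to "and/or diagnosis of emotional disorders according to ADIS-5 interview". Section 2.4.1 says of the ADIS-5: "In this trial, this interview will be used to assess eligibility criteria to participate in the trial".

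**Schedule.** Section 2.4 states that "Table 2 shows the measures used in each phase of the study". In that table the Eligibility column holds only the ADIS-5, the sociodemographic data and the COVID-19 symptoms. OASIS and ODSIS first appear at Pre, then at Baseline, Treatment, Post and the follow-ups.

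**Order.** Section 2.3 says: "If inclusion criteria are accomplished, participants will receive the pre-assessment protocol through e-mail". It then says: "Once the pre-assessment is completed, each participant will be sequentially and randomly assigned to one of the three multiple baseline conditions". The baseline days and the intervention follow. The opening sentence of section 2.4 lists baseline ahead of pre-assessment, the reverse of section 2.3 and of Table 2's columns.

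**Analysis.** The hypothesis at the end of the Introduction is improvement from pre-assessment to post-assessment. The repeated measures ANOVA in section 2.6 examines "differences between the pre-treatment and the remaining assessments in the outcome variables", within each baseline condition. The daily baseline series is used in the visual analysis only, and section 2.4.2 changes its recall window from the last week to the previous day.

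**The concern.** There are two linked problems.

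First, a score threshold is part of the entry rule, but no scheduled administration precedes Pre. Either a screening administration is missing from Table 2, or the Pre score does the selecting, which contradicts section 2.3. The reader cannot tell which.

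Second, section 2.1 justifies having no control group on the ground that participants act as their own controls. In a multiple-baseline design, the baseline phase is what provides that control. Here the only planned inferential within-person contrast starts from a score taken before that phase. Symptom change while patients wait for session 1 then becomes part of the reported effect, over a period that differs by condition. If symptoms ease during the wait, the error favours the hypothesis; if they worsen, it goes the other way. The comparison between conditions cannot remove it, because all three conditions receive the same intervention and none stays untreated.

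**Working it through.** **The plan's own figure.** The only calculated number is the 60 participants in section 2.2.2 (effect size 0.3, power 80%). A paired two-sided test at an assumed alpha of 0.05 gives ((1.96 + 0.84)/0.3)² ≈ 87.2, so 88, not 60. However, the article states no alpha, test or within-person correlation, so this does not show 60 to be wrong. The present point does not depend on it.

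**Step 1: which score meets the cut-off?**

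| Source | What it implies |
|---|---|
| Table 1 | an OASIS/ODSIS score, or an ADIS-5 diagnosis, is known at entry |
| Table 2 | the first OASIS/ODSIS is at Pre |
| Section 2.3 | Pre is sent only after the criteria are met |

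All three cannot be complete as written. The ADIS-5 route resolves this only for patients who enter by diagnosis.

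**Step 2: untreated change in the contrast.** Let b be the average untreated change per day. From Pre to the end of baseline the contrast absorbs at least 6b, 8b or 10b, according to condition. With 20 patients per condition the average is (6 + 8 + 10)/3 = 8 days, so 8b. The conditions differ by up to 10b − 6b = 4b with no difference in treatment. The article gives no value for b, so this part cannot be sized. It applies whichever score was used for screening.

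**Step 3: regression to the mean, only if Pre is also the screen.** The inputs are assumptions, since the article gives no SD or retest figure: retest correlation ρ of 0.6 to 0.9; cut-off from 1 SD below to 0.5 SD above the mean of the screened population; observed correlation of 0.6 between the scales; everyone entering by the cut-offs; no treatment effect.

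For selection on a single scale at standardised cut-off c, the expected fall in SD units is (1 − ρ)·φ(c)/(1 − Φ(c)):

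- c = −1, ρ = 0.9: 0.1 × 0.288 = 0.03
- c = 0, ρ = 0.6: 0.4 × 0.798 = 0.32
- c = 0.5, ρ = 0.6: 0.4 × 1.141 = 0.46

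The trial admits on either scale, which weakens selection on each. A simulation of 400,000 patients (true score plus independent error) gives the following fall per scale in SD units. In brackets is the chance of a significant two-sided paired t test at n = 60, nominally 5%.

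| Cut-off relative to mean | ρ = 0.6 | ρ = 0.7 | ρ = 0.8 | ρ = 0.9 |
|---|---|---|---|---|
| −1 SD | 0.03 (6%) | 0.02 (6%) | 0.02 (5%) | 0.01 (5%) |
| −0.5 SD | 0.07 (9%) | 0.05 (8%) | 0.04 (7%) | 0.02 (6%) |
| at the mean | 0.12 (17%) | 0.09 (14%) | 0.06 (12%) | 0.03 (8%) |
| +0.5 SD | 0.19 (36%) | 0.15 (29%) | 0.10 (21%) | 0.05 (13%) |

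Entry by ADIS-5 diagnosis alone reduces these figures.

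**Step 4: the same model with a separate screening score.** Selecting on one administration and measuring Pre on another, with independent errors, gives a Pre-to-Post fall of 0.00 SD in every cell. The regression has already happened before Pre.

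**The case against.** A reader might infer that the cut-offs alone decide entry, that Pre must be the score they are applied to, and that the pre-post effect is therefore inflated by regression to the mean. The article does not support this. Table 1 also admits by ADIS-5 diagnosis, so a patient below both cut-offs can enter. Section 2.3 has patients who meet Table 1 sign consent with the nursing team, then take the ADIS-5 call, and only then receive the pre-assessment. The simpler reading is that Table 2 omits a screening administration, and Figure 1, which is not available here, may show it. Nor should the single-scale figures in step 3 be taken as the expected bias: selection on one scale is not the entry rule.

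It can also be said that the baseline is not ignored. The visual analysis sets it against the treatment phase and the follow-ups, and would show marked drift. The conditions differ by at most four days, and section 2.1 calls the study a pilot. All of this is true, but visual inspection on a previous-day recall window does not correct a last-week pre-post estimate, and the hypothesis is stated as significant improvement from Pre.

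Finally, a last-week form just before session 1 reaches back over the whole of a 6-day baseline, so it does not isolate the last baseline day. That stands. It still describes the baseline phase, which is the design's control, instead of the week before it.

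**Conclusion.** The point holds in two unconditional parts and one conditional part.

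- **Unconditional:** Tables 1 and 2 and section 2.3 together do not show which OASIS/ODSIS administration is tested against the cut-offs, and sections 2.3 and 2.4 disagree on the order of baseline and pre-assessment.
- **Unconditional:** the within-person inference is anchored before at least 6, 8 or 10 untreated days, so change in that time is credited to the intervention. Its size and sign cannot be derived from the article.
- **Conditional on Pre being the screening score:** regression to the mean adds roughly 0.01 to 0.19 SD per scale and raises the chance of a spurious significant pre-post difference to between 5% and 36%. These ranges rest entirely on the assumptions in step 3. With a separate screen and independent errors the addition is about zero.

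This should be corrected. It does not show that the trial's effect estimate will be materially wrong.

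**What to change.** 1. Mark the screening OASIS/ODSIS administration in the Eligibility column of Table 2, and use that score for selection only.
2. Reconcile the order of baseline and pre-assessment in the text of section 2.4 with section 2.3 and Table 2.
3. For OASIS and ODSIS, define the pre-treatment reference in section 2.6 as a standard last-week form completed immediately before session 1. If the first weekly treatment-phase form is taken then, it can serve; otherwise add one form.
4. Report the change from Pre to session 1 as untreated change, beside the change from session 1 onwards.

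The cost is at most one 10-item online form through the existing Google Forms route, and possibly a slightly smaller reported effect. Two limits remain and should be stated as limitations: natural change during the treatment phase is still uncontrolled, and MEDI, EuroQol-5D, DERS and DTS remain referenced to Pre.
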